### Randomization and blinding

Previous consent to participate will be solicited for the director of each cluster (medical director of the ICU, nursing coordinator of the ICU) and for nursing staff that will perform the intervention.

All the ICUs participants will be randomized (ratio 1:1) to be assigned to either an intervention group (an indication of repositioning every 2 h) or to conventional care (Intervention provided by care providers using a non-standardized frequency of repositioning). The randomization will be set in the main execution center of the study, which is Fundación Cardioinfantil located in Bogotá, and will be computerized with random numbers. Besides, randomization will be executed using a permutation design by blocks of two possible combinations (intervention A or B). The allocation will be openly announced in each hospital. The study will be blind to evaluators (internal analysts and statisticians) [16, 19, 20]. Furthermore, following this, we plan to apply a consent form for the patients [or their parents according to their health status] when admitted to the ICU.

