### Inclusion and exclusion criteria

Criteria for clusters (ICUs) inclusion: ICUs that admit adult patients (≥ 18 years) in critical condition, with any type of care emphasis (surgical, medical, neurological, or a mixture of any), with a minimum of 10 beds, that submit the feasibility survey and agree to commit to the care assigned in the randomization until including the total number of the sample. At least one ICU will be included from each hospital. In case one hospital may participate with more than one ICU, the units should have to receive the same allocation resulting from the randomization.

Criteria for clusters exclusion: intermediate care units or coronary care units in which patients are self-mobilized; or critical units for burned patients. Also, units destined for the care of patients with Covid 19 in which the standard of repositioning is between every 12–16 h.

Criteria for patient inclusion in each cluster: all patients are eligible as long as they are completely unable to move, have their skin intact at the moment of their admission into the ICU, are care-dependent for their complete mobilization (including unconsciousness, being under sedation or assisted ventilation), and are scheduled for a hospitalization period of at least 48 h.

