The Hazard Ratio is an estimate that derives from the Cox model, and this is from the rate of risk index between the groups that received a higher frequency rate of postural changes than the groups that received conventional care of postural changes. An adjusted analysis by co-variables will be developed considering the related risk factors in the literature for developing PUs (age and comorbidity). The safety outcomes will be described as the registered events regarding posture shifts in each branch according to their frequency level in interventions A or B, and the association between posture shifts and their compilations will be explored. To detect early differences in the occurrence of events amongst the groups, we planned two interim analyses; once the 33 and 66% of the units are randomized, these internal analyses will be made using the sequential method [23].

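### Permuted blocks that read as blocks of two, with ICUs randomized over time, let anyone who knows earlier allocations deduce the second one in each block before the next hospital enters

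*Protocol article*

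**What the plan says.** Under Randomization and blinding, the protocol article states "All the ICUs participants will be randomized (ratio 1:1"). The list is made at the main execution center and "will be computerized with random numbers". The method is that "randomization will be executed using a permutation design by blocks of two possible combinations (intervention A or B"). On disclosure it says "The allocation will be openly announced in each hospital", and on masking "The study will be blind to evaluators (internal analysts and statisticians").

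Under Statistical analysis, two interim looks are planned: "once the 33 and 66% of the units are randomized, these internal analyses will be made using the sequential method". Setting gives about 36 months for the whole study and 3–4 months of recruitment per ICU.

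Under Inclusion and exclusion criteria, ICUs must "agree to commit to the care assigned in the randomization until including the total number of the sample", and all ICUs of one hospital receive the same arm. Data collection and procedure adds that hospitals come from a list of 60–100, that a feasibility survey and a prior discussion help to settle eligibility, and that directors consent beforehand to the randomized care.

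**The concern.** At 1:1, a permuted block with exactly two possible orderings has size two. Once the first place is known, the second follows with certainty. If hospitals enter one after another, the person deciding which hospital goes forward next, or when, could know the arm it will get.

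In a cluster trial that opens a route to selection bias at the level where randomization is meant to protect. Units expected to have a low or a high ulcer rate could be matched, even unintentionally, to the known arm. With 22 units in all, a few such placements carry weight. The only masking described concerns analysts and statisticians, which acts after allocation and does not hide the next assignment.

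**Working it through.** **Inputs.** From Sample size: 22 ICUs, 150 patients each, control incidence 0.075, intervention incidence 0.023, intra-class correlation (ICC) 0.035, power 80%. Alpha is taken as 0.05 two-sided (assumption; it is printed as a percentage and sidedness is not stated). From Randomization and blinding: 1:1 and the block wording. From Statistical analysis: looks at 33% and 66% of units randomized.

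**The plan's own figure.** 22 × 150 = 3,300, so 11 ICUs per arm. The usual two-proportion formula for 0.075 against 0.023 gives 270 per arm. The design effect is 1 + 149 × 0.035 = 6.215, and 2 × 270 × 6.215 = 3,356, close to 3,300. Sample size is not affected by this point; the check confirms the number of units.

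**Block size from the wording.** The number of orderings of a 1:1 block is 2 for size two, 6 for size four and 20 for size six. Only size two fits two possible combinations.

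**Timing.** 0.33 × 22 = 7.3 and 0.66 × 22 = 14.5. At the first look about 7 units are randomized and about 15 are not, so a single randomization of all units is hard to square with the text. Randomization in batches is compatible with it.

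**Predictability if allocations are released one at a time and block size and earlier allocations are known.** In a block of size b, the expected share of places forced by earlier ones is 1/(b/2 + 1). The share guessed correctly comes from always naming the arm with more places left. For size two that is (0.5 + 1)/2 = 75%.

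| Block size | Forced places, of 22 | Guessed correctly, of 22 |
|---|---|---|
| 2 | 11.0 (50%) | 16.5 (75%) |
| 4 | 7.3 (33%) | 15.6 (71%) |
| 6 | 5.5 (25%) | 15.0 (68%) |
| 22 (one balanced list) | 1.8 (8%) | 13.5 (61%) |

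Rows for sizes 4 and 6 scale the block shares to 22. A larger block of known, fixed size helps only modestly; withholding and varying the size, or fixing the set of hospitals before any allocation is released, does most of the work.

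**Several ICUs per hospital.** If the hospital is the unit and H hospitals enter, H/2 allocations (rounded down) are forced. H is not given; for an assumed H of 16 to 22 that is 8 to 11. If the list instead runs over ICUs, a second ICU in a hospital takes the first one's arm and is known in advance, whatever the block.

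**What steering could do (illustration, assumed degree).** On the proportion scale the plan's ICC implies a between-ICU standard deviation of √(0.035 × 0.075 × 0.925) = 0.049, or 4.9 percentage points. The difference in the sample-size inputs is 7.5 − 2.3 = 5.2 points. With 11 forced places, about half of each arm is forced on average. If those units were shifted by k standard deviations in opposite directions, the arm difference would move by 2 × 0.5 × k × 4.9 points: 1.2 for k = 0.25 and 2.5 for k = 0.5, against 5.2. Nothing in the protocol says that k differs from zero.

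**The case against.** The case against is substantial, and much of it limits the point.

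- **Block size.** The bracket in the sentence names the two arms, not two orderings, so it may only mean permuted blocks over two interventions. This stands as an ambiguity. Even so, blocks of two is the most natural reading and the only scheme the article describes.
- **Sequential entry.** It rests on one clause about interim timing. The clause does imply randomization over time, but not hospital by hospital; batches would also fit.
- **Open announcement.** This may mean only that each hospital hears its own arm, which an unblinded nursing intervention requires. That stands. The exposure then lies with people who know several allocations, not with every hospital.
- **Prior commitment.** It is already planned and limits refusal after allocation. It does not govern which hospital on the list of 60–100 goes next, or when.
- **Condensed article.** Concealment details may sit in the full protocol, so their absence here is no finding. The block rule, however, is stated, and it is the stated rule that is weak.

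A reader might infer more: that concealment is certainly lost for exactly half the units, that the coordinating center both holds the list and picks the hospitals, or that the background incidence of 3.3% to 52.9% shows how far these ICUs differ. The documents support none of these. The count depends on the block reading and on how many ICUs each hospital brings. Randomization is placed at the main center, but no section says who recruits or schedules hospitals. The incidence range is worldwide.

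**Conclusion.** The point holds as a risk. It assumes that the blocks are of size two, that allocations are released over time within blocks, and that someone who knows earlier allocations influences which hospital enters next or when. The first is the natural reading and release over time is implied; the third is not stated either way. Under all three, up to 11 of 22 allocations can be deduced beforehand if each ICU is allocated separately, with a different count under the same-hospital rule. No bias is shown, and none of this says that anyone would use the knowledge. The change is still worth making, because a stated rule can be replaced by a safer one at almost no cost.

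**What to change.** Replace the blocks of two. Make the hospital the unit of randomization, in line with the same-hospital rule. Randomize hospitals that have already committed, in one batch or a few large batches, so that the set is closed before any arm is known. Batches can be kept compatible with the planned looks at a third and two thirds of units.

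If hospitals must enter one by one, use larger, randomly varying block sizes, withheld from everyone who recruits or schedules hospitals. Register each hospital irrevocably before its allocation is released. The planned advance commitment covers part of this; what it lacks is a fixed order of entry.

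The cost is a new list and either a short wait to form a batch or a possible imbalance of one or two units. Sample size and the interventions do not change.

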### Design of Intervention

#### Intervention group a (frequent repositioning ≤ to every 2 h)

The intervention group received a repositioning with a frequency interval which we call “high-frequency” to be applied to every admitted patient consecutively, at a level that is lesser than or equal to every 2 h in a 24/h span (this is with a minimum goal of 8–12 position shifts in 24 h minus 2 o 3 at night to prevent altering the patients’ circadian rhythm). Changes in position will be executed so that patients go from a lateral-right position to a supine position, and later a lateral-left position; or from a lateral-right position to a lateral-left position or vice versa; or from a supine position to a prone position or vice versa [only if this repositioning is provided every 2 h]. The supine position can be overlooked as long as the postural shift is made at the indicated time.

#### Control group B (conventional care)

The units randomized to this care will be labeled as conventional care will not implement any intervention. Patients in this group will receive the usual care for repositioning applied at any frequency.

Furthermore, patients from both groups will receive all other interventions that are currently applied in their hospitals regarding the prevention of PUs according to their hospital’s protocols. Additionally, repositioning will be performed according to routine practices related to initiation, interruption, re-initiation, or finalization of posture changes, depending on the state of health of each patient, medical orders, and nursing decisions. Patients recruited in each ICU will be follow up when they develop their first PU (stage I), or when they begin the autonomous mobilization [ambulation], or when they are transferred to service to another hospital, or they discharge to their homes, or if they die in the ICU.

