**Methods:**

A nurse-applied cluster randomized controlled trial of parallel groups (two branches), in which 22 eligible ICUs (each consisting of 150 patients), will be randomized to a high-frequency level repositioning intervention or to a conventional care (control group). Patients will be followed until their exit from each cluster. The primary result of this study is originated by regarding pressure ulcers using clusters (number of first ulcers per patient, at the early stage of progression, first one acquired after admission for 1000 days). The secondary results include evaluating the risk index on the patients’ level (Hazard ratio, 95% IC) and a description of repositioning complications. Two interim analyses will be performed through the course of this study. A statistical difference between the groups < 0.05 in the main outcome, the progression of ulcers due to pressure (best or worst outcome in the experimental group), will determine whether the study should be put to a halt/determine the termination of the study.

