In addition to this, there is no evidence of possible complications associated with different mobilization frequencies [7]. Studies on routinely preventive interventions, such as the postural shifts and their efficacy in care for patients at high risk for ulcers in ICUs, deserve to be revised carefully. This study aims to solve any uncertainty that exists over what repositioning frequency in static patients best reduces PUs and the possible complications of such interventions. We have planned to perform a pressure ulcer prevention study by nursing in its second phase (PENFUP phase 2). We hypothesize that more frequent repositioning (≤ to every 2 h) performed by nursing staff and critical patients is more effective in reducing the development of pressure ulcers than any other conventional repositioning (applied less frequently ≥ to every 4 h).

Therefore, we have developed a cluster randomized controlled clinical trial that is also multi-centric, pragmatic, and double-blind, made up of two branches comparing a frequent repositioning intervention of 2 h or less with a group of conventional care.

The specific aim is to evaluate the efficacy in preventing PUs acquired during hospitalization on two frequency levels of repositioning or posture shifts in adult patients in different ICUs (clusters) in different regions across Colombia. The three specific aims of this study are 1) to evaluate the efficacy in the intervention of greater frequency, relative to the group of conventional care in the emergence of pressure ulcers and secondary outcomes by clusters; 2) to analyze the hazard ratio (HR) of patients included in the repositioning group of greater frequency compared to the group of patients included in the conventional group in the development of their first PU during their stay in ICUs, and 3) to describe complications related to changes in the position of patients in different ICUs of different hospitals across Colombia.

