### Data collection and procedure

Various hospitals from different regions of Colombia will be recruited from a list of 60–100, each of which will be handed a feasibility survey and a prior discussion, which will help decide each hospital’s eligibility for entering the study. Any hospital that decides that the study is allowed to proceed in its facilities (depending on board matters, nurse-patient relationship, and prior consent to execute interventions resulting from randomization, approval from the medical director and nursing director with a prior protocol explanation) agrees and commits to participating in the study and executing the designated intervention. Having decided which hospitals are eligible, the study will be sent to their own board of ethics committees for careful evaluation and approval.

If this is the case and to proceed with the study, the medical director and nursing director must sign a consent form and all involved nursing staff based on the hospitals’ ethics committee demands. Patients will also be required to sign a document of informed consent to authorize the registration of relevant data regarding their health and medical record. Once each hospital is familiar with the assigned intervention**,** all involved staff will receive instructions for the study implementation and its procedures to be applied in their respective ICUs.

Each intervention will be executed by healthcare staff (nurses and nursing assistants) consecutively according to the allocated intervention in all patients until reaching the study sample in each ICU (150 patients). For ensuring the consistency of the interventions, the total of postural shifts per ICU, in all frequencies, will be recorded daily during a span of 3 months along the course of the intervention by a data collector from patient’s charts from both groups.

A patient will remain in the study from the moment of admission into the ICU until he or she is either transferred to another service or another hospital center, begins walking, or ambulation develops a pressure ulcer or dies.

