	Care guide or policy Institutional Preventive (Yes-No) Name of guideline				N (%)			
	Professional Nurses per shift				Median ó mean (interquartile range IQR)			
	Auxiliares per shift				Median ó mean (interquartile range, IQR)			
**1–4 Months by ICU**	**T1√**	**T2√**	**T3√**	**T4√**	**T1√**	**T2√**	**T3√**	**T4√**
**6-Intervention Characteristic**	Adherence in ICU to intervention				Compliance day by day (yes = 1, no = 2) % compliance (calculated from 80% days stay per patient) ▪ Number of times one patient is mobilized in the intervention ▪ Description of the teams (total number of people who mobilized the patient) ▪ Total number of teams repeating intervention per shift ▪ The number of head and auxiliary nurses per team.			
	Acceptance of the final intervention of the study				Evaluation of the acceptability of the intervention by the personnel			
	Description of usual or conventional care by ICU				Descriptive Individual __or group__ Frequency per shift__ Position variation: yes_ No_ Descriptive.			

If by any chance (including medical assessment or clinical practice setbacks), patient mobilization is decided to be avoided, patients will be excluded from adherence to the intervention (temporarily or definitely), given the pragmatic nature of the study. This information will be registered on the platform. Regular follow-up will be ensured to verify if data is submitted completely and coherently. This will be done by the platform coordinator of PENFUP phase 2. When a pressure ulcer is detected, the nurse in charge of each patient will report it in the individual medical record and will assess the depth of each wound (Fig. 2. SPIRIT figure of study timeline).

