### Statistical analysis

All ICUs shall be analyzed according to the branch they were randomized to (Intention to treat) [7, 23]. The incidence of PU will be analyzed considering the time of natural first appearance; that is, within the time-lapse in which the patients are in the study. The two-time variables to be considered for this analysis will be admission into the ICU and the emergence of PUs since the time of admission for each patient. Also, we will include the length of stay in the ICU. The characteristics of the clusters and each individual will be analyzed considering counts (%), means (SD), medians (interquartile range). The percentage of applied interventions (repositioning) by clusters in each group will be computed according to the total of interventions that should be administered in both branches of high frequency and conventional care. The primary analysis will be done at the cluster level (ICU) and the secondary at an individual level (each patient). When analyzing at a cluster level, the total number of PUs will be divided by the total of accumulated days of each patient in each cluster to obtain incidence rates in both groups; this is done based on the permanence of the patients from each cluster. To calculate the incidence rate (IR of 95%), the incidence rate in the groups with a higher frequency of postural changes in group A will be divided by the control groups’ incidence rate of postural changes in group B. The incidence of PU will be analyzed considering the time of natural first appearance; that is, within the time-lapse in which the patients are in the study.

The secondary result includes evaluating the frequency of the severity of PUs (stages I - IV) and will be compared with both groups using an adjusted Chi-square test. For the individual evaluation of the risk of PUs in patients, the first PU to appear in each patient will be considered for calculating the rate of events and time before the event. The hazard ratio (HR) will be computed using Cox proportional-hazard models and its corresponding 95% confidence intervals (CI), adjusted by the standard error by cluster (SE) [23]. The Cox models will be implemented for exploring relations between the main result and the explanatory considering the time before the time of occurrence.

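### The article contradicts itself on when follow-up ends, and a stop at the first ulcer would reduce the planned stage I–IV comparison to stage at first detection

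*Protocol article*

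**What the plan says.** **End of follow-up.** Four places bear on it.
- Abstract, Methods: "Patients will be followed until their exit from each cluster".
- Control group B, in a paragraph that covers both arms: "Patients recruited in each ICU will be follow up when they develop their first PU (stage I), or when they begin the autonomous mobilization". Transfer, discharge home and death in the ICU follow as further endpoints. The verb is garbled, and I read it as follow-up until the first of these events.
- Data collection and procedure: a patient leaves the study on transfer or when he or she "begins walking, or ambulation develops a pressure ulcer or dies".
- Table 1: the dates at which follow-up may end are first ambulation, transfer within or between hospitals, and death. A pressure ulcer is not among them. The same table collects ICU length of stay from admission to discharge, and ICU complications including death, without restricting either to ulcer-free patients.

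**Event and stage.** The Abstract defines the primary outcome by the "number of first ulcers per patient, at the early stage of progression". The Outcomes section counts new ulcers of any grade from I to IV, and Table 1 tabulates ulcers by stage. Statistical analysis plans a secondary result "evaluating the frequency of the severity of PUs (stages I - IV) and will be compared with both groups" by an adjusted chi-square test.

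**Who judges.** Once an ulcer has been found, "the nurse in charge of each patient will report it in the individual medical record and will assess the depth of each wound". Randomization and blinding states: "The allocation will be openly announced in each hospital". That section and Study design mask only those who analyse the data. The Background nevertheless calls the trial "multi-centric, pragmatic, and double-blind".

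**The concern.** The plan wants two things from each patient: a first-event time, for which observation may stop at the first ulcer, and a description of severity and safety, for which it should not. If participation ends at the first ulcer, a lesion recorded at stage I keeps that stage for good, whatever happens to it later. The severity comparison then reflects how early ulcers are noticed as well as how bad they become.

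Earliness of notice may differ by arm. The intervention aims for at least 8 to 12 position changes in 24 hours, while control patients are turned at whatever frequency is usual, so the chances to see the skin may differ. Earlier detection at stage I in one arm could then pass for milder disease. Stage I is also the stage most open to judgement: the classification section defines it as erythema on unbroken skin that does not blanch. The person judging it delivers an intervention known to everyone on the unit.

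Complications and deaths after the ulcer would also go unrecorded, more often in the arm with more ulcers.

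**Working it through.** **1. The texts side by side.** Control group B and Data collection and procedure stop at an ulcer. The Abstract and Table 1 do not. The two sides could be reconciled by letting the ulcer end at-risk time for the first-event analysis while recording continues to ICU exit, but the article does not say so. The primary rate is affected too: Statistical analysis divides ulcers by accumulated patient-days, and that total depends on whether days after an ulcer count.

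**2. What the stop does to the stage comparison.** A first ulcer seen at stage I is recorded as I, and later progression is not observed. A first ulcer seen at stage II, III or IV is recorded at that stage. The chi-square test therefore compares stage at first detection. It is not empty, but it is not worst severity.

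**3. The planning figures.** Inputs from Sample size: 22 ICUs of 150 patients, control incidence 0.075, intervention incidence 0.023 (or a 50% reduction, 0.075 × 0.5 = 0.0375), ICC 0.035, power 80%, and alpha read as 0.05 two-sided.
- Design effect: 1 + (150 − 1) × 0.035 = 6.215.
- Individuals per arm for 0.075 against 0.023: (1.960 + 0.842)² × (0.075 × 0.925 + 0.023 × 0.977) / 0.052² = 266.6.
- Total: 2 × 266.6 × 6.215 = 3,314, close to the stated 22 × 150 = 3,300. The pooled-variance formula gives 270 per arm and 3,356.

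With 11 ICUs per arm there are 1,650 patients per arm. The stated 50% reduction does not reproduce 3,300, which is a separate matter; both intervention rates are carried below.

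**4. Patients cut short under the stop.**
- Control: 1,650 × 0.075 = 124 (7.5%).
- Intervention: 1,650 × 0.023 = 38 (2.3%), or 1,650 × 0.0375 = 62 (3.75%).
- Ratio between arms: 7.5/2.3 = 3.3, or 7.5/3.75 = 2.

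**5. Patient-time lost.** Assume that each of these patients loses 25% to 75% of the stay, and that stays are equally long with and without an ulcer. Neither figure is in the article.
- Control: 0.075 × 0.25 to 0.075 × 0.75 = 1.9% to 5.6%.
- Intervention at 0.023: 0.6% to 1.7%. At 0.0375: 0.9% to 2.8%.
- Effect on the primary rate ratio at 0.023 if at-risk days stop at the ulcer and do not run on: a factor of (1 − 0.01875)/(1 − 0.00575) = 0.99 to (1 − 0.05625)/(1 − 0.01725) = 0.96.

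**6. Stage II or worse at first detection.** The share *s* of first ulcers found at stage II or worse is not given, so it is varied and taken as equal in both arms. Events are 1,650 × rate × *s*. Power uses the two-proportion normal approximation with 1,650/6.215 = 265 effective patients per arm and the same ICC. For all stages it gives 79.4% at 0.023.

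| *s* | Control events | Intervention events (0.023 / 0.0375) | Power (0.023 / 0.0375) |
|---|---|---|---|
| 10% | 12.4 | 3.8 / 6.2 | 14% / 8% |
| 25% | 30.9 | 9.5 / 15.5 | 27% / 15% |
| 50% | 61.9 | 19.0 / 30.9 | 49% / 26% |
| 75% | 92.8 | 28.5 / 46.4 | 67% / 36% |

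The analysis can be done but is weak, and it omits every stage I ulcer that later worsens.

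**7. Unblinded calling of stage I, for illustration.** Assume no true effect, a stage I share of 50% to 80% of first ulcers, and a 20% relative difference between arms in calling stage I. The apparent rate ratio is 1 ± share × 0.20: 0.90 to 0.84 for under-calling in the intervention arm, 1.10 to 1.16 for over-calling. Both inputs are assumptions.

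**The case against.** The strongest reply is that nothing need be lost. Table 1 gives no ulcer among its end dates and collects length of stay, complications and death for the whole ICU stay; the Abstract follows patients to exit. On that reading the ulcer closes only the first-event clock. The reading is possible, and for that reason truncation cannot be stated as fact. It does not remove the defect, because Data collection and procedure makes a pressure ulcer a reason for leaving the study.

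A reader might infer that the stop makes any analysis of stage II or worse impossible. It does not: Outcomes counts grades I to IV, Table 1 tabulates by stage, and the nurse assesses each wound's depth. What is lost is progression after a recorded stage I ulcer.

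A reader might also take 0.84 to 1.16 as the bias in the primary result. The article supports neither input, the two directions oppose each other, and the under-calling side is an extreme: a stage I lesion that is missed and then progresses would still be counted later as a first ulcer.

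It is fair to add that open delivery is hard to avoid when whole units change how nurses reposition patients, and that Study design and Randomization and blinding describe the masking correctly. The Background label is a wording error. The safety loss is also small, and safety is planned as description and exploration.

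**Conclusion.** The contradiction on end of follow-up is firm and must be resolved. The rest is conditional on the stop being applied. In that case:
- the stage I–IV comparison measures stage at first detection by nurses who know the allocation;
- analysis of stage II or worse is limited to ulcers first found at that stage, with 14% to 67% power at the 0.023 planning rate for assumed shares of 10% to 75%, and less at a 50% reduction;
- safety follow-up is shortened for up to 7.5% of control against 2.3% to 3.75% of intervention patients.

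That last loss is small, but two to three times as common in the control arm and caused by the outcome itself. No net bias in the primary rate ratio is shown. Nor would stage II or worse be an objective endpoint, since the same nurse grades it. Independently of the follow-up rule, the double-blind label is wrong on the article's own description.

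**What to change.** - Reconcile the Abstract, Control group B, Data collection and procedure, and Table 1 on the end of follow-up.
- Keep the first pressure ulcer of any stage as the primary event, and state that at-risk time ends there for both the incidence rate and the Cox model.
- Continue to record worst ulcer stage, complications and death until ICU exit in every patient, through the existing data collectors.
- Base the severity comparison on worst stage reached.
- Pre-specify a supportive analysis of first ulcer of stage II or worse, and say that it is still graded unblinded and has lower power than the primary analysis. Independent or masked confirmation of ulcers, where feasible, would strengthen it.
- In the Background, replace double-blind with open-label, analyst-blinded.

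The cost is protocol wording and a little extra charting for the few percent of patients who develop an ulcer. Independent confirmation, if chosen, would cost more. The primary event and the sample size do not change.
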